# Robotic-based ACTive somatoSENSory (Act.Sens) retraining on upper limb functions with chronic stroke survivors: study protocol for a pilot randomised controlled trial

**DOI:** 10.1186/s40814-021-00948-3

**Published:** 2021-11-15

**Keywords:** Proprioception, Kinaesthesia, Robot-assisted training, Haptic guidance, Reward feedback

## Abstract

**Background:**

Prior studies have established that senses of the limb position in space (proprioception and kinaesthesia) are important for motor control and learning. Although nearly one-half of stroke patients have impairment in the ability to sense their movements, somatosensory retraining focusing on proprioception and kinaesthesia is often overlooked. Interventions that simultaneously target motor and somatosensory components are thought to be useful for relearning somatosensory functions while increasing mobility of the affected limb. For over a decade, robotic technology has been incorporated in stroke rehabilitation for more controlled therapy intensity, duration, and frequency. This pilot randomised controlled trial introduces a compact robotic-based upper-limb reaching task that retrains proprioception and kinaesthesia concurrently.

**Methods:**

Thirty first-ever chronic stroke survivors (> 6-month post-stroke) will be randomly assigned to either a treatment or a control group. Over a 5-week period, the treatment group will receive 15 training sessions for about an hour per session. Robot-generated haptic guidance will be provided along the movement path as somatosensory cues while moving. Audio-visual feedback will appear following every successful movement as a reward. For the same duration, the control group will complete similar robotic training but without the vision occluded and robot-generated cues. Baseline, post-day 1, and post-day 30 assessments will be performed, where the last two sessions will be conducted after the last training session. Robotic-based performance indices and clinical assessments of upper limb functions after stroke will be used to acquire primary and secondary outcome measures respectively. This work will provide insights into the feasibility of such robot-assisted training clinically.

**Discussion:**

The current work presents a study protocol to retrain upper-limb somatosensory and motor functions using robot-based rehabilitation for community-dwelling stroke survivors. The training promotes active use of the affected arm while at the same time enhances somatosensory input through augmented feedback. The outcomes of this study will provide preliminary data and help inform the clinicians on the feasibility and practicality of the proposed exercise.

**Trial registration:**

ClinicalTrials.gov NCT04490655. Registered 29 July 2020.

**Supplementary Information:**

The online version contains supplementary material available at 10.1186/s40814-021-00948-3.

## Introduction

Stroke is among the top three leading causes of long-term disability worldwide [1]. The resulting impairment of motor functions, particularly in the upper limb (UL), may lead to dependency in activities of daily living (ADL) [2, 3]. In addition to motor impairments, approximately 50% of stroke survivors also suffer from somatosensory impairments, which have a significant and long-lasting impact on their motor recovery and quality of life [4–7]. For example, Carey, Matyas and Baum [7] revealed that stroke survivors with somatosensory loss showed a significant decrease in retained participation across the domains of instrumental, social and physical leisure activities, compared to those without somatosensory loss.

Despite the scarce evidence, training paradigms that simultaneously combine both motor and somatosensory components are thought to be more beneficial for stroke survivors [8–10] owing to the significant correlation between the two impairments following stroke [11]. Hence, these forms of training paradigm are useful for relearning somatosensory functions while increasing the mobility of the affected UL, since stroke survivors with UL impairments are less likely to use their hands, which subsequently leads to reduced sensory processing in their UL [12].

Proprioception and kinaesthesia are the senses that provide sensory information of limb position in space. Studies in healthy adults have demonstrated the importance of passive training of proprioception in motor learning, where such training is useful for enhancing and facilitating motor performance and learning [13–16]. In stroke survivors, there is evidence highlighting the role of proprioception as a predictor for motor relearning [17, 18]. For instance, the extent of motor relearning is associated with proprioceptive impairment, in which damage to the somatosensory areas in the brain could impair learning ability and thus interfere with the recovery of sensory-guided movements [19]. A randomised controlled trial (RCT) with a variety of tactile and proprioceptive training has shown that such forms of intervention are helpful for the recovery of sensation after stroke [20]. Given the importance of proprioception in motor control and learning, the retraining of tactile sensation alone after stroke may not be sufficient to improve UL motor functions [21]. Accordingly, the inclusion of somatosensory-based training focusing on proprioception and kinaesthesia deserves more attention, while its role as an integral part of a stroke rehabilitation programme is often overshadowed by motor-based therapy.

To date, the use of robotic technology has shown great promise in the domain of stroke rehabilitation research [22, 23]. Robotic technology has also gained popularity for assessing UL somatosensory functions (proprioception and kinaesthesia) due to its objective quantification of performance and high interrater reliability [24–27]. Indeed, the use of robotic devices in stroke rehabilitation is clinically attractive as it can achieve more controlled therapy intensity, duration, and frequency. Specifically, robotic-based training of proprioception in chronic stroke survivors has been examined in [28]. In fact, a single session of passive somatosensory discrimination task is able to induce plasticity in the sensorimotor networks of the brain that correlate with the initial impairment [29].

The purpose of the current work is twofold. First, we assess whether the robotic-based intervention that integrates somatosensory components into the motor task can reliably bring benefits to stroke survivors compared to motor training alone. While some earlier studies emphasised the tactile or haptic aspects of distal joints [20, 21], this work focuses on the proprioception, kinaesthesia, and movement-induced cutaneous sensation of proximal joints (elbow and shoulder). The proposed task promotes active use of the affected UL of the participants, while at the same time enhances somatosensory information through haptic guidance, unlike some prior studies which use a purely passive discrimination task (e.g. in [29]). Second, the results of this study will be valuable to estimate the effect size and to inform a decision for larger-scale multi-centre studies in the future, since the existing evidence of similar training paradigms is still insufficient [9]. Taken together, this work will add to the knowledge of the feasibility and benefits of a combined robotic-based somatosensory and motor retraining post-stroke.

## Methods/design

### Study design

An intensive robotic-based behavioural training for chronic stroke survivors, with emphases on retraining of proprioception and kinaesthesia, will be conducted. This is a two-arm RCT consisting of treatment and control groups. Participants are chronic stroke survivors from the local community in Singapore who will go through a series of training using their affected UL for 15 regular sessions. Each session will take place every alternate day, 3 days per week, for 5 weeks. On top of the training sessions, three behavioural and clinical assessments will be performed at baseline, post-day 1, and post-day 30, where the follow-up assessments will happen the following day and 30 days after the last training session respectively. All assessments will be administered by a therapist who is blinded to treatment allocation throughout the study. This therapist is different from the person who will be responsible for the routine intervention. Prior to the commencement of the study, the principal investigator will provide a half-day training session to the therapists involved. The process flow of this study is outlined in Fig 1, and the timeline of recruitment and enrolment processes, interventions, and study visits is summarised in the Standard Protocol Items: Recommendations for Interventional Trials (SPIRIT) diagram (Fig 2). This study was designed following the guidelines of the SPIRIT 2013 checklist (see Additional file 1).

**Fig. 1 Fig1:**
[figure not shown]
Diagram of study flow

**Fig. 2 Fig2:**
[figure not shown]
SPIRIT diagram of the schedule of enrolment, interventions, and outcome measures. Abbreviations: *FMA-UE* Fugl-Meyer Assessment for Upper Extremity, *WMFT* streamlined Wolf Motor Function Test, *EmNSA* Erasmus MC modifications to the Nottingham Sensory Assessment, *MAS* modified Ashworth scale of spasticity

### Participants

First-ever ischemic or haemorrhagic stroke survivors of at least 6-month post-stroke, between the ages of 21 and 75 years will be recruited from the local community rehabilitation centres. Stroke survivors with sensory impairment as assessed by the Erasmus MC modifications to the Nottingham Sensory Assessment (EmNSA) (each category ≤ 6/8), shoulder abduction and elbow extension of motor power grade > 2 as rated by the Medical Research Council (MRC) scale for muscle strength will be considered eligible to participate. However, those with bilateral impairment, high upper-limb spasticity (modified Ashworth scale of spasticity > 2), unilateral neglect as assessed by Star Cancellation Test (score < 44), cognitive impairment as examined by Mini-Mental State Examination (< 26/30), known history of mental disorders, and the inability to perform upper limb activity due to excessive pain will be excluded. Eligible participants will be randomly assigned to either a treatment group or a control group by a study team member not involved in the training or assessment. Block randomisation technique will be used to generate an allocation list with equal allocation ratio. Following this, the allocation list will be revealed in sealed envelopes to the therapist before the first training session. Participants in both groups who have completed the full study will receive financial compensation ($40/session) at the end of the last assessment session.

Potential participants will be recruited via face-to-face contact by on-site therapists who are part of the study team, where study rationale, potential benefits and time commitment will be introduced. This intervention would replace the UL therapy session of the participants on that specific day. However, they will not be asked to stop any UL intervention on the days they are not attending our programme. They may withdraw at any time from their participation for any reason and without any negative consequences for their rehabilitation in the future. To ensure a low dropout rate, all participants will be given a list of their scheduled visit in advance and followed up regularly by the study team through phone calls as a reminder of their upcoming visit. The study team will also keep a record of participant attendance to track the retention rate, and other UL exercises that the participants have been doing.

### Sample size

To estimate the sample size for this study, a Cohen’s *d* effect size of 0.5 was applied with a statistical power of 0.80 and an alpha level of 0.05. The resulting estimate is 28 participants in total based on the statistical power analysis programme G*Power (version 3.1.9.7). Approximately 36 participants will be screened and recruited, where 30 subjects will be estimated to complete the full study (with a conservative dropout rate of 20%).

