### Statistical analysis

All statistical analyses will be carried out using SPSS (ver. 28.0). Information obtained from the primary and secondary assessments will be recorded as text files. From the motor test data, different kinematic parameters will be computed: endpoint error and smoothness. Likewise, kinaesthetic performance will be estimated by the difference between the reference trajectory produced by the robot and the reproduced trajectory by the participants. Behavioural outcomes obtained from every training session will be computed to identify the improvements in kinematic parameters session by session: total number of successful outcomes and average endpoint error in reaching trajectories. Due to its superiority in analysing repeated-measures dataset with and without missing values, a mixed-effects model with random intercepts and slopes will be used to reveal significant differences in the outcome measures between the two groups over three time points (baseline, post day 1, and post day 30). Statistical significance will be based on *p* value threshold of 0.05. Any post hoc comparisons will be performed following the main analysis using Tukey’s tests. Cohen’s *d* will be employed to estimate the effect size of the change scores for this study. Questionnaire results will be reported via descriptive statistics (frequency analysis).

All results will be presented with 95% confidence intervals.

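### 28 to 30 participants in two arms give about 25% power for a between-group Cohen's d of 0.5, not the stated 80%; 80% power is reached only at d of about 1.06 to 1.10

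*Protocol article*

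**What the plan says.** The Sample size section of the protocol article states an "effect size of 0.5 was applied with a statistical power of 0.80 and an alpha level of 0.05" and continues: "The resulting estimate is 28 participants in total based on the statistical power analysis programme" (G*Power is the programme named). About 36 are to be recruited so that 30 complete. The section gives no test, sidedness, number of measurements or correlation.

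The rest of the article fixes the comparison:

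- Study design: "This is a two-arm RCT consisting of treatment and control groups". The Participants section adds equal allocation.
- Introduction: the first aim is to find out whether adding somatosensory components does better than motor training by itself. The second is to estimate an effect size and inform the decision on larger multi-centre studies.
- Statistical analysis: a mixed-effects model compares the two groups over baseline, post-day 1 and post-day 30 at a 0.05 threshold, and Cohen's d "will be employed to estimate the effect size of the change scores for this study".

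**The concern.** Cohen's d is a difference in means divided by a standard deviation. In a two-arm trial whose first aim is a between-group benefit, a reader will take d = 0.5 as a half-SD difference between the arms. Detecting that with 80% power in 14 per arm is far from the familiar result for two independent groups, so either the sample size or the effect size is wrongly described.

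The power statement matters even in a pilot. The protocol tests group differences at 0.05 and says the results will feed the decision on a larger trial. If true power for d = 0.5 is about one in four, a real effect of that size would be missed about three times in four. A reader who believed the stated 80% could take a non-significant result as evidence that somatosensory retraining adds nothing to motor training. Carrying the pairing of d = 0.5 with 28 participants into the next trial would undersize that trial too.

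**Working it through.** **Inputs.** From Sample size: d = 0.5, power 0.80, alpha 0.05, N = 28, 30 completers. From Study design and Participants: two arms, 1:1. From Statistical analysis: three time points, d on change scores. Sidedness is not stated, so both were tried.

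**1. Reproducing 28.** Take the repeated-measures within-between interaction test with f = d/2 = 0.25, 2 groups, m = 3 measurements, correlation ρ = 0.5 and sphericity. The test family, f and ρ are assumptions; the article gives none of them.

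- λ = f²·N·m/(1 − ρ), with df = 2 and (N − 2)·2.
- N = 28: λ = 0.0625 × 28 × 3 / 0.5 = 10.5, df (2, 52), power 0.812.
- N = 26: λ = 9.75, df (2, 48), power 0.778.

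The smallest even N reaching 0.80 is 28, which matches the article.

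**2. What f = 0.25 means as a group difference.** Let the group differences at the three visits be (0, D, D), a gain kept to day 30. Each group's interaction effects are half the deviations from the mean difference, (−2D/3, D/3, D/3)/2, with sum of squares D²/6. Over both groups and six cells:

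f² = (2 × D²/6)/6 = D²/18, so f = 0.2357·D.

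Setting f = 0.25 gives D = 1.06 SD. For (0, D, D/2), a gain half lost by day 30, f² = D²/24, so f = 0.2041·D and D = 1.22 SD. In this test, therefore, halving d does not give f: d = 0.5 kept to day 30 corresponds to f = 0.118.

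**3. Two-arm comparison of change scores (noncentral t).** Noncentrality = d·√(n/2), df = 2n − 2.

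| n per arm | Power at d = 0.5, two-sided | One-sided | Detectable d at 80% power, two-sided |
|---|---|---|---|
| 14 | 0.247 | 0.361 | 1.10 |
| 15 | 0.262 | 0.379 | 1.06 |
| 18 (all 36 recruited) | 0.308 | 0.431 | 0.96 |

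For 80% power at d = 0.5: 64 per arm (128 in total) two-sided, power 0.801; 51 per arm (102) one-sided, power 0.806.

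**4. The 2 × 3 interaction with d = 0.5.** If d is in change-score SD units, D = d·√(2(1 − ρ)). Then λ = (D²/18)·3N/(1 − ρ) = d²·N/3, so ρ cancels.

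- N = 28: λ = 0.25 × 28/3 = 2.33, power 0.245.
- N = 30: λ = 2.50, power 0.261.
- Detectable d at 80% power: 1.05 (N = 28) or 1.01 (N = 30).

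If d is in raw-score SD units, ρ matters. Power at N = 28:

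| ρ | 0 | 0.3 | 0.5 | 0.7 | 0.8 | 0.9 |
|---|---|---|---|---|---|---|
| Power | 0.14 | 0.19 | 0.25 | 0.39 | 0.55 | 0.85 |

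Power crosses 0.80 at ρ of about 0.89. At ρ = 0.5, 80% power needs 118 participants in total.

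**5. Paired test.** With d = 0.5, a one-sided paired t-test needs 27 and a two-sided one 34. The first is close to 28, but it tests change within one group and cannot compare the arms.

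**The case against.** The strongest reply is that 28 is probably genuine software output for a design that resembles the planned one (two groups, three time points), so this is not an arithmetic slip. That stands: the fault most likely lies in describing f = 0.25 as d = 0.5. It does not rescue the statement, because the effect then powered for is about twice the one named.

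A second reply is that the 25% comes from a t-test on change scores, whereas the plan is a mixed model, and that the Sample size section does not say its d refers to change scores. The sentence on change scores concerns reporting after the trial. This is fair as far as it goes: on a raw-score reading the answer depends on a correlation the article does not give. A contrast of the mean of both follow-ups against baseline is more efficient than the interaction test. With a 0.5 raw-SD difference at both follow-ups, the contrast has variance 1.5(1 − ρ), which gives power at 15 per arm of 0.33 at ρ = 0.5, 0.67 at 0.8 and about 0.80 at 0.85. So 80% needs a correlation of roughly 0.85 to 0.89 or more, and nothing in the article supports one. The value 0.5 that reproduces 28 is well below that range.

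A third reply is that this is a pilot, that results will carry 95% confidence intervals, and that nothing says a null result will be read as no benefit. That lowers the stakes and makes the misreading a risk rather than a certainty. But a pilot need not claim power at all; this one claims 80%, and the claim should be true. Leaving out the software settings is normal in an article and is not itself the fault.

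**Conclusion.** The concern holds. For a between-group d of 0.5 in change scores, two-sided alpha 0.05, power is about 25% with 28 participants and 26% with 30, against a stated 80%. The t-test and the 2 × 3 interaction agree on this within rounding. The effect detectable with 80% power is d = 1.10 (28) or 1.06 (30) by t-test, and 1.05 or 1.01 by the interaction test when the gain is kept to day 30.

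These figures assume equal arms and d on the change-score scale used in the Statistical analysis section. On a raw-score scale, interaction power with 28 runs from 0.14 to 0.55 for correlations from 0 to 0.8. The explanation of where 28 came from is an inference, but the conclusion does not depend on it. The statement is wrong as written and must be corrected; the size of the trial need not change.

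**What to change.** Keep the enrolment and replace the power statement in the Sample size section with, for example:

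> Thirty completers (15 per arm) give 80% power at two-sided alpha 0.05 for a between-group difference in change of d of about 1.06; power for d = 0.5 is about 26%. The size was chosen for a pilot: the 95% confidence interval for d will have a half-width of about 0.72.

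The half-width is 1.96 × √(2/15) = 0.716 for d near zero. Adding d²/(2 × 30) under the root gives 0.73 at d = 0.5 and 0.76 at d = 1.06.

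If the investigators prefer to keep the calculation behind 28, they should report the effect size on the scale actually entered and translate it into a between-group difference. If the settings were those inferred here, that means f = 0.25, three measurements and correlation 0.5, or about 1.06 SD if the gain is kept to day 30. Naming the G*Power test and inputs in the same sentence would settle the matter.

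The cost is one reworded paragraph and a less favourable stated power. No participants, visits or analyses are added.

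### The number randomised is stated inconsistently: the abstract randomises 30, while the sample size section makes 30 the completers out of about 36 recruited

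*Protocol article*

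**What the plan says.** The Sample size section of the protocol article takes a Cohen's d with "effect size of 0.5 was applied with a statistical power of 0.80 and an alpha level of 0.05" and reports the G*Power result: "The resulting estimate is 28 participants in total". It continues: "Approximately 36 participants will be screened and recruited", of whom "30 subjects will be estimated to complete the full study (with a conservative dropout rate of 20" per cent).

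The Methods paragraph of the abstract states that "Thirty first-ever chronic stroke survivors" will be randomly assigned to the two groups.

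The Participants section describes block randomisation of eligible participants in equal ratio and gives no number. The study flow diagram (Fig. 1) is not reproduced in the text at hand, so it cannot be used to settle the matter.

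**The concern.** The figure 30 has two roles. In the abstract it is the number entering randomisation. In the Sample size section it is the number left at the end, after a loss from about 36. With a 20% dropout rate one group of 30 cannot be both.

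The Sample size section also treats screening and recruitment as one step with one number, so it does not say how many of the 36 reach randomisation. The number randomised determines the length of the allocation list and whether the target of 28 is protected against dropout, so it should be stated once and clearly.

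A smaller problem sits alongside: 36, 30 and 20% do not agree with each other under the usual meaning of a dropout rate.

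**Working it through.** **Inputs.** From the Sample size section: required total 28, recruited about 36, expected completers 30, dropout 20%. From the abstract: 30 randomised.

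**Reproducing the plan's 36.** Multiplying the completers by one plus the dropout rate gives 30 × 1.2 = 36, exactly the stated figure. Allowing for dropout properly means dividing by the retained fraction: 30 / 0.8 = 37.5, rounded up to 38.

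**The stated loss.** 1 − 30/36 = 0.167, so going from 36 to 30 is a loss of about 17%, not 20%.

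**Completers under each reading, at 20% dropout after randomisation:**

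| Number randomised | Completers | Against 28 required |
|---|---|---|
| 36 (all those recruited) | 36 × 0.8 = 28.8 | met |
| 30 (abstract) | 30 × 0.8 = 24 | 4 short |

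**Number needed.** 28 / 0.8 = 35 randomised for 28 completers, so 36 is enough if all 36 are randomised.

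**Illustration of power.** The Sample size section names no test, number of measurements or correlation. I assumed a repeated-measures group-by-time interaction F test with f = d/2 = 0.25, two groups, m = 3 measurements, correlation ρ = 0.5 and sphericity. The noncentrality is λ = N × m × f² / (1 − ρ), with (m − 1) and (N − 2)(m − 1) degrees of freedom.

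- N = 28: λ = 28 × 3 × 0.0625 / 0.5 = 10.5 on 2 and 52 df; power 0.81.
- N = 26: power 0.78. So 28 is the smallest even total reaching 0.80, and these assumptions can reproduce the protocol's figure.
- N = 24: λ = 9.0 on 2 and 44 df; power 0.74.

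The result depends heavily on the assumed correlation. At N = 24 power is about 0.58 for ρ = 0.3 and about 0.93 for ρ = 0.7. Reproducing 28 does not show that this was the calculation used.

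**The case against.** The strongest reply is that little follows from this in practice. The Sample size section calls 36 approximate. At 20% dropout it yields 28.8 completers, only 1.2 fewer than stated and still above 28. That stands, and for this reason the dropout slip should not lead the point.

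A second reply is that the abstract may simply report the expected study size, or that some of the six lost are screening failures, so no shortfall need arise. This stands in part: the shortfall to 24 arises only if 30 is the working number and the full 20% is lost after randomisation. But the inconsistency remains on either explanation. If the abstract means completers, it is wrong to call them randomised. If the six are screening failures, nothing in the 36 allows for dropout among the 30 randomised. The Participants section speaks of dropout in connection with participants who have scheduled visits, which points to loss during the study.

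A reader might infer that the trial will end with 24 completers and will be underpowered at 0.74. The documents do not support that. They do not say that the abstract's figure governs enrolment. The power figure rests on inputs the protocol does not give. The Statistical analysis section plans a mixed-effects model chosen partly for its handling of missing values, so participants who drop out after contributing some data are not lost to the analysis. The study is also a pilot, with estimation of the effect size among its aims. A reader might equally infer that 36 are randomised, 18 per arm; no section says so.

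**Conclusion.** The point holds as an inconsistency in a key design number. The abstract randomises 30; the Sample size section makes 30 the completers from about 36 recruited; nothing else in the text resolves it.

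If 30 are randomised and 20% then drop out, 24 complete, four below 28. If 36 are randomised, about 28 to 29 complete, which meets 28 but is not the stated 30. Both counts take the protocol's 20% as loss after randomisation and need no further assumption. The power values of 0.81 and 0.74 are illustrative only.

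The dropout allowance is wrong as written but harmless by itself. The conflict over the number randomised should be corrected.

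**What to change.** - State one number randomised, the same in the abstract and the Sample size section, and give the number to be screened separately.
- Choose it to fit the protocol's own target: at 20% dropout after randomisation at least 35 are needed for 28 completers, so 36 suffices if all 36 are randomised. To keep 30 completers at 20%, 38 would be needed.
- If 36 is kept as the number randomised, change the expected completers from 30 to about 28 to 29, or keep 30 and give the dropout rate as about 17%.

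If the 36 were always meant to be randomised, this is a change of wording only. If the 36 include people who fail screening, randomising 35 or 36 means screening more than 36, and that recruitment effort is the real cost.
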